**Figure 1 F1:**
[figure not shown]
Timeline of this study.

**Table 2 T2:** Schedule of enrollment, interventions, and assessments.

	**Part 1**			**Part 2**	**Part 3**
	**Enrollment**	**Visit 1**	**Visit 2**	**Visit 3**	**Visit 4^a^)**
Timeline	Diagnosis of stroke	During hospital stay	Before rehabilitation	End of intervention	Follow-up
	Admission				
	Day 0 + 3 days	Day 3 + 3	Day 7 ± 3	Day 28 ± 3	3 months ± 7 days
Check for inclusion/exclusion criteria	X				
Randomization	X				
Informed consent^b^	X				
Baseline data	X				
Neurological assessment	X		X	X	X
Edinburgh Handedness Inventory (EHI)	X				
(p)mRS	X		X	X	X
NIHSS	X	X	X	X	X
BI	X		X	X	X
LAST	X	X	X	X	X
ACL	X	X	X	X	X
BIAS	X	X	X	X	X
BDI	X		X	X	X
(EQ-5D-5L)	X		X	X	X
Evaluation of self-training (h/day)		X	X	X	X

a *Alternative: phone call if personal consultation is not possible*.

b *If not able to get permission from the patients themselves, their legal guardian will have to give written informed consent for their contribution*.

*ACL, Aphasia Check List; BDI, Beck Depression Inventory; BIAS, Bielefelder Aphasie Screening; BI, Barthel Index; CNS, central nervous system; mRS, modified Rankin-Scale; NIHSS, National Institutes of Health Stroke Scale; LAST, Language Screening Test*.

The group with Neolexon® will receive logopedic therapy with the help of Neolexon® (exercise programs for speech therapists in the program, therapist app version). The control group will receive standard speech therapy without Neolexon®. Both groups will be instructed in self-training in the control group without the help of the app and in the treatment group with Neolexon®. In both groups, the frequency, duration, and type of self-training will be documented. The total study duration is 12 weeks and is divided into three parts:

Part 1 consists of screening and enrollment in the study. Part 1 will take place in our facility at the acute phase of ischemic or hemorrhagic stroke for ~1 week and includes two study visits: visit 1 and visit 2. During study visit 1, initial baseline information, including demographic, epidemiologic, and clinical data as well as comorbidities, are obtained, including neurological assessment using various screening tools at inclusion, aphasia rating scales as well as patient questionnaires for quality of life and depression. It is important to note that clinical examinations will take place outside the regular study visits at day 14 and 21 and potentially before a change of location.Part 2 of our trial concludes after discharge to a rehabilitation facility. Visit 3 will be performed in this context. On this occasion, the abovementioned tests and psychological questionnaires from the enrollment are repeated. Visit 3 will take place ~4 weeks after screening as a follow-up visit.Between visit 3 and visit 4, the intensity of the intervention (self-exercises, speech therapy) is assessed, but there is no longer any need to comply with randomization.

Part 3 of the study includes the follow-up after 3 months: Clinical follow-up will be obtained during an outpatient clinic visit as an endpoint-blinded design, If this is not possible, telephone follow-up will be assessed.

As for the neurological examination, information including etiology of stroke or specific therapy regimens is collected. The severity of the stroke will be measured throughout using the (premorbid) modified Ranking-Scale (pmRS/mRS) (22), the National Health Institute of Stroke Scale (NIHSS) (23), as well as the Barthel Index (BI) as a well-known instrument describing independence for daily life skills. Scoring 100 means fully capable of self-care whereas 0 implies the opposite (24).

Screening for aphasia will be performed using the Language Screening Test (LAST) (25, 26). The LAST is a simple, quick, validated screening instrument focusing on speech comprehension, word repetition, and naming. LAST is conducted using the following parts: “Naming,” “Repetition,” “Automatic speech,” “Picture recognition,” and “Verbal instructions.” A total score of 15 can be achieved, meaning one point per item. The minimum number of points that can be attained is 0 (25, 26). In clinical trials, there is no validation of severity of aphasia using the LAST; however, based on clinical experience and consensus, the severity of aphasia is as follows: 0–5 severe, 6–10 moderate, and 11–14 minimal.

The Aphasia Check List (ACL), developed by Kalbe et al. (27) comprises two main parts: The first part, “Language,” covers a broad range of linguistic aspects, i.e., speaking in series or reading out loud. Communication abilities are evaluated on the basis of a four-level rating scale: From 0 meaning “severe aphasia” to 3 implying lack of disability. Also, writing after dictation is one noteworthy subtest. The second part, “Cognition,” focuses on non-verbal recall using tasks that require logical thinking, attention, and memory. After adding up all subtests, a cutoff score at 135 is defined as aphasia. The ACL takes up to 30 min (27). The ACL is a test that actually allows the severity of aphasia to be quantified. It is known to have test–retest reliability, and it has been used in other studies. However, the ACL does not include all the important speech/language modalities, so the primary endpoint is determined using the Bielefelder Aphasie Screening (BIAS).

The primary endpoint of the study is examined using the BIAS to assess the severity and course of aphasia in general as well as in subitems (28). The BIAS is a diagnostic tool that can be administered in the acute phase within 20–40 min with relatively little effort in clinical routine depending on aphasia severity. The BIAS addresses all modalities of language, from reading comprehension to spontaneous speech. The latter is used at the beginning of the evaluation as a first assessment. Aphasia is judged based on the performance in the seven subscales: 1. Spontaneous speech, 2. Auditory comprehension, 3. Automatic language use, 4. Semantic lexical performance 5. Reading comprehension, 6. Writing of words. All subtests are documented on a protocol sheet and scores are added up at the end. Finally, the severity of aphasia is graded using a percentile rank (PR) from 100%, which refers to a healthy person, to 0% (28).

Furthermore, as depression and reduced quality of life are common comorbidities in patients with stroke, patient-reported outcomes using the EuroQol 5 dimensions and 5 level version (EQ-5D-5L) and Beck's Depression Inventory (BDI-II) will be recorded with the help of a trained speech-language therapist or neuropsychologist. The EQ-5D-5L is a self-administered questionnaire to evaluate the quality of life. It is a standardized measure of health status providing a simple, generic measure of health for clinical and economic appraisal and consisting of two parts—the EQ-5D descriptive system and the EQ visual analog scale (EQ-VAS). The EQ-5D-5L descriptive system comprises the following five dimensions: mobility, self-care, usual activities, pain/discomfort, and anxiety/depression. Each dimension has five levels: no problems, slight problems, moderate problems, severe problems, and extreme problems (29).

The BDI-II is a multiple-choice self-report inventory for measuring the severity of depression and is composed of items related to symptoms of depression such as hopelessness and irritability, emotions such as guilt or feelings of being punished, as well as physical symptoms such as fatigue, weight loss, and lack of interest in sex (30).

### Data Analysis

Results from the study assessments will be recorded in a paper-based case report form (CRF). This form includes all the abovementioned screening tools plus questionnaires, and the survey of the intensity and frequency of applied speech therapy as well as (self-)training lessons. It is intended that each anonymous CRF will be filled in by our staff (speech therapists, doctoral candidates, or physicians) and then transferred either directly or afterwards into a central database on our server, so that the responsible individuals have parallel access to the data to maintain them. The paper form is collected and stored closed at the same time at our facility.

#### Primary Objective

Based on the consensus in our study team, we considered a 10% mean difference in the change of the PR of BIAS to be a minimal and clinically important difference. Our primary objective is to demonstrate a significant improvement of 10% in BIAS comparing the two groups. Differences in quality of life, BDI, and mRS will we evaluated as secondary outcome parameters.

We aimed to recruit 180 participants (90 patients per group), which had 85% power for a 5% two-sided test to address the primary objective. Sample size was adjusted for an assumed dropout rate of ~20%; therefore, at least 144 patients (72 per group) should be analyzed. We expect about 50% of screen fails—based on the calculated sample size, we need to screen 360 patients in our stroke unit.

Data with normal distribution will be presented as mean ± standard deviation (SD), and non-normally distributed data will be presented as median and range (min, max) or interquartile range (IQR). For categorical variables, counts and percentages will be given. Data will be compared with the chi-square test, Mann–Whitney test, or Student's *t*-test where appropriate. A two-sided *p*-value of <0.05 will be considered statistically significant. Binary logistic regression models will be used to analyze the association between study group and outcome parameters. Results will be adjusted for well-known outcome predictors after stroke, e.g., age, sex, NIHSS, pmRS, lesion size, treatment, comorbidities, and complications. Statistical analysis will be performed with the Statistical Package for the Social Sciences, SPSS (SPSS Inc., 21.0 for Windows).

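### The only covariate-adjusted model named for the outcomes is binary logistic regression, so the adjusted analysis of mRS, a graded scale, must split it in two and discards shifts that do not cross the cut

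*Protocol article*

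**What the plan says.** All the relevant analysis text is in the protocol article under Data Analysis, Primary Objective.

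- **Outcome.** "Differences in quality of life, BDI, and mRS will we evaluated as secondary outcome parameters". Table 2 schedules (p)mRS at enrolment and at Visits 2, 3 and 4.
- **Unadjusted comparison.** "Data will be compared with the chi-square test, Mann–Whitney test" or Student's t-test, whichever is appropriate.
- **Adjusted model.** "Binary logistic regression models will be used to analyze the association between study group and outcome parameters". No ordinal or linear model is named.
- **Covariates.** "Results will be adjusted for well-known outcome predictors after stroke, e.g., age, sex, NIHSS, pmRS, lesion size, treatment, comorbidities, and complications".
- **Size.** "at least 144 patients (72 per group) should be analyzed". The power statement is limited to the main question: "which had 85% power for a 5% two-sided test to address the primary objective".

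No effect size, expected distribution, cut or power is given for mRS.

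**The concern.** The section calls mRS, BDI and quality of life outcome parameters, and the regression sentence uses the same term, so it reaches mRS. The adjustment list, with NIHSS and premorbid mRS in it, also fits a functional stroke outcome. A binary logistic model needs a two-level response. Once mRS is split, a patient who moves from 5 to 3, or from 1 to 0, contributes nothing if both grades lie on the same side of the cut.

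At stake is the adjusted estimate of the effect on function. It allows for baseline severity, and an unadjusted rank test cannot supply it. The Discussion accepts that the study could be underpowered, so giving up information on a named outcome is hard to justify when a model for ordered data is available.

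**Working it through.** **1. The plan's own figures.** The dropout arithmetic is consistent: 180 × 0.8 = 144 and 72 / 0.8 = 90. The 85% power concerns BIAS and cannot be derived from stated inputs, because no SD is given. Solving 72 = 2(1.960 + 1.036)² / d² gives d = 0.50, so the figure implies an SD of about 20 for a 10-point difference. None of this bears on mRS. Only the 72 per group is carried forward.

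**2. Inputs for mRS.** From the document: 72 per group, 1:1 allocation, two-sided 5%. Assumed: proportional odds, a common odds ratio (OR) for better outcome, and a control distribution.

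**3. Worked example.** Assume OR = 2.0 and equal control probabilities of 1/7 in each grade 0 to 6.

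*Full scale* (Whitehead's proportional-odds formula). The information is V = n₁n₂N(1 − Σp̄³) / [3(N + 1)²], where p̄ is the category probability averaged over the arms, and power = Φ(ln OR × √V − 1.96).
- The treated-arm probabilities are 0.250, 0.194, 0.156, 0.127, 0.106, 0.090 and 0.077, so 1 − Σp̄³ = 0.977.
- V = 72 × 72 × 144 × 0.977 / (3 × 145²) = 11.56.
- 0.693 × 3.400 − 1.96 = 0.397, so power is 65.4%.

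*Split scale.* Power = Φ[(|p₂ − p₁| − 1.96 s₀) / s₁], where s₀ is the pooled and s₁ the unpooled standard error.
- Cut 0–1: p₁ = 0.286 and p₂ = 0.444. (0.1587 − 1.96 × 0.0802) / 0.0791 = 0.02, so power is 50.7%. The loss is 14.7 points.
- Cut 0–2: p₁ = 0.429 and p₂ = 0.600. (0.1714 − 1.96 × 0.0833) / 0.0821 = 0.10, so power is 54.0%. The loss is 11.4 points.

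**4. Range.** The same formulas were applied to six assumed control distributions: mild, middle, flat, severe, restricted to grades 0–4, and clustered.

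| Assumed OR | Full-scale power | Loss at cut 0–1 | Loss at cut 0–2 |
|---|---|---|---|
| 1.5 | 25–28% | 3–15 points | 5–11 points |
| 2.0 | 59–65% | 7–32 points | 11–28 points |
| 2.5 | 82–88% | 7–33 points | 10–37 points |
| 3.0 | 93–96% | 5–24 points | 6–36 points |

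The loss is small when the cut falls near the middle of the distribution and large when it falls in a tail. A Mann–Whitney simulation (4,000 runs, middle distribution, OR 2.0) agrees: 66% on the full scale against 50% (cut 0–1) and 57% (cut 0–2).

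**5. Does the loss persist after adjustment?** Steps 3 and 4 compare unadjusted analyses. Covariate-adjusted models were therefore also simulated at 72 per group, with three assumed distributions, one assumed prognostic covariate and 300 runs per scenario. The Monte Carlo standard error is at most √(0.25/300), about 2.9 points.
- OR 2.0: adjusted ordinal 59–66%, adjusted binary 30–49%.
- OR 1.5: adjusted ordinal 24–28%, adjusted binary 13–19%.

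The adjusted ordinal model also had more power than the unadjusted Mann–Whitney test in every scenario.

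**The case against.** The strongest reply is that the plan already holds a full-scale test. Mann–Whitney is listed two sentences before the regression model and needs no cut. A reader might infer that mRS must be split in every analysis; the text does not support that. This part of the reply stands, and it confines the point to the adjusted analysis. It does not remove it. The tests are listed for use where appropriate, so Mann–Whitney is not tied to mRS, and it gives no estimate adjusted for premorbid mRS, NIHSS or the aphasia-severity stratum.

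A second reply is that the cut may be in an analysis plan that is not shown. That also stands. A reader might infer that the cut is open to choice after the data are seen, with an inflated false-positive rate if several are tried. Nothing in the document says that several cuts would be tried, so no such claim is made. Fixing the cut would not restore the lost information, however, and an ordinal model in the analysis plan would depart from the model that the article names.

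A third reply is that a split mRS is a familiar supplement and a responder rate is easy to explain. That is fair, and is a reason to keep one split as a supportive analysis.

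**Conclusion.** The point holds for the adjusted analysis of mRS only. The article names a model that does not fit an ordered outcome, and an adjusted proportional-odds model would use the same data better.

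The size is conditional. At 72 per group, under proportional odds, with assumed common ORs of 1.5 to 3.0 and assumed control distributions, the loss is roughly 3 to 37 points of power at cuts 0–1 and 0–2. A single headline loss would be tempting, but the document gives no mRS effect or distribution to support one, and losses below 10 points are common at OR 1.5 or with a well-placed cut. The range comes from unadjusted formulas; the smaller adjusted simulation points the same way.

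No stated figure is wrong. mRS is a secondary outcome and the 85% power claim does not cover it. The change should be made, but the trial's main conclusion does not depend on it.

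**What to change.** In the Primary Objective section, after the list of tests, state that:

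- the adjusted analysis of mRS uses a proportional-odds (ordinal logistic) model over the full scale;
- it adjusts for pre-treatment covariates: premorbid mRS, enrolment NIHSS and the aphasia-severity stratum used in randomisation;
- the result is reported as a common odds ratio with its 95% confidence interval;
- binary logistic regression is kept for binary outcomes, or for one supportive mRS split at a cut set in advance.

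The regression sentence fits the continuous scores no better, so the same edit can name a model for each type of outcome. A linear model for those scores would not by itself repair mRS.

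The cost is a sentence or two and no new data. The proportional-odds assumption has to be checked, and a common odds ratio is slightly less intuitive than a responder rate.

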### Selection/Treatment of Subjects

Patients fulfilling the inclusion criteria at screening will be randomized in a ratio of 1:1 into two comparative treatment groups. Patients not capable of giving written informed consent due to physical or mental disorders can be included in the study after written informed consent of the legal guardian. On the other hand, if the inability to give permission is transient, the patient has to acquiesce afterwards.

The procedure considers stratification by aphasia severity to ensure balanced strata, maintaining allocation concealment. The Medical Informatics, Biometry, and Epidemiology (IBE) of the University of Munich will provide an internet-based, password-protected randomization tool “Randoulette^4^,” which chooses the treatment sequence for a new patient who fulfills the eligibility criteria and has signed the informed consent. Randoulette will register the patient by his or her screening number, gender, year of birth, and strata before the allocated number is provided.

Patients will be screened directly after admission to hospital for stroke. The study population includes a broad range of patients with acute aphasia after any stroke (ischemic or hemorrhagic). Inclusion and exclusion criteria are shown in Table 1.

**Table 1 T1:** Inclusion and exclusion criteria for Lexi study.

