One of the potential limitations of our work is that only patients with post-stroke aphasia are included. There will be no conclusive data from aphasia after other causes. In addition, we decided not to investigate chronic aphasia. However, we are considering the possibility of performing further trials on these topics. Non-fluent German speakers and severely affected patients who are unable to use the tablet-based app due to the fact that physical or mental conditions are excluded, as are patients with a reduced life expectancy. Due to the lack of previous studies, we cannot conduct a sample size calculation based on treatment effects. Thus, this study could be underpowered to show an effect in the interventional group.

Our goal is to show whether patients could benefit from Neolexon® computer-based speech therapy. Further studies might be necessary to approach the main problem of other aspects of aphasia. Other important factors that could be interesting to analyze are motivation for speech therapy, reducing negative affective symptoms during treatment, and lower workload for other family members (43).

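### No analysis is fixed for the BIAS mean difference, and the only adjusted model named, binary logistic regression, cannot estimate it

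*Protocol article*

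**What the plan says.** All of this is in the protocol article.

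- **Target quantity** (Primary Objective): "we considered a 10% mean difference in the change of the PR of BIAS to be a minimal and clinically important difference". The description of BIAS under Interventional Methods gives the scale: "the severity of aphasia is graded using a percentile rank (PR) from 100%, which refers to a healthy person, to 0".
- **Sample size** (Primary Objective): "We aimed to recruit 180 participants (90 patients per group"), "which had 85% power for a 5% two-sided test to address the primary objective". Then: "Sample size was adjusted for an assumed dropout rate of ~20%; therefore, at least 144 patients (72 per group) should be analyzed".
- **Tests** (Primary Objective): chi-square, Mann–Whitney or t-test, whichever suits the data.
- **Adjusted model** (Primary Objective): "Binary logistic regression models will be used to analyze the association between study group and outcome parameters". Results are to be adjusted for known predictors of stroke outcome. The list is given as examples and includes age, sex, NIHSS and premorbid mRS. Neither BIAS at enrolment nor aphasia severity is in it.
- **Randomisation** (Selection/Treatment of Subjects): "The procedure considers stratification by aphasia severity to ensure balanced strata, maintaining allocation concealment".
- **Prognosis** (Discussion): outcome is said to depend on initial aphasia severity and on the stroke itself, while age and sex appear unrelated to it.
- **Data collected** (Table 2): BIAS is scheduled at enrolment and at every later visit.

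**The concern.** The planned effect is a difference between two means on a 0 to 100 scale. Of the methods named, only the t-test estimates it. Mann–Whitney does not test a mean difference unless further assumptions are made. Binary logistic regression works on a yes/no outcome and gives an odds ratio, so BIAS would first have to be cut at a threshold that the article does not state.

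The article also promises adjusted results, and none of the three simple tests can adjust for covariates. Read as written, an adjusted result for BIAS could come only from the logistic model. Two things are at stake. The analysis that decides the trial is left open, including a possible cut-point chosen after the data are seen. And the covariate that the Discussion treats as prognostic, initial aphasia severity, is not put to use.

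**Working it through.** **1. Reproduce the stated sample size.** Inputs from Primary Objective: two-sided 5%, 85% power, difference 10 points, 72 analysed per group, about 20% dropout. The SD of change is not given; the Discussion says "Due to the lack of previous studies, we cannot conduct a sample size calculation based on treatment effects". It therefore has to be assumed.

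- Dropout: 144 / 0.8 = 180 and 72 / 0.8 = 90. Both match.
- Back-solved SD: 10 × √(72/2) / (1.960 + 1.036) = 60 / 2.996 = 20.0.
- Check at SD 20: standard error = 20 × √(2/72) = 3.333; 10 / 3.333 = 3.00; power = Φ(3.00 − 1.96) = 85.1% (84.6% with the noncentral t).

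So 72 per group fits a comparison of mean change with SD about 20. Because the SD is back-solved, this shows consistency and does not confirm the 85%. At 72 per group the same test has 97.9% power at SD 15, 67.0% at SD 25 and 51.6% at SD 30.

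**2. Mann–Whitney, same assumptions, normal data.** With relative efficiency 3/π, power is 83.4%. Little power is lost, but the test does not estimate the mean difference.

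**3. If BIAS change were dichotomised.** This step is hypothetical. Changes are assumed normal with SD 20, the control mean is set at 0 and the app-group mean at 10, and two proportions are compared with 72 per group.

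| Cut (points above control mean) | Control | App group | Power | n per group for 85% |
|---|---|---|---|---|
| 5 (midway between the means) | 40.1% | 59.9% | 66% | 114 |
| 0 | 50.0% | 69.1% | 65% | 117 |
| 10 | 30.9% | 50.0% | 65% | 117 |
| 20 | 15.9% | 30.9% | 57% | 142 |

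For the first row: (0.1974 − 1.96 × 0.0833) / 0.0817 = 0.417, and Φ(0.417) = 66%. Even the most favourable of these cuts needs 114 analysed per group, against 90 recruited.

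**4. If baseline BIAS is used as a covariate.** Let σ be the SD of BIAS at each visit, assumed equal, and r the baseline/follow-up correlation. The variance of change is 2σ²(1 − r). The ANCOVA residual variance is σ²(1 − r²). Their ratio is (1 + r)/2.

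| r | Variance ratio | Effective SD = 20 × √ratio | Power, 72 per group | n per group for 85% |
|---|---|---|---|---|
| 0.3 | 0.65 | 16.1 | 96.1% | 47 |
| 0.5 | 0.75 | 17.3 | 93.4% | 54 |
| 0.7 | 0.85 | 18.4 | 90.2% | 62 |
| 0.8 | 0.90 | 19.0 | 88.5% | 65 |

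For r = 0.7: 10 / (18.44 × √(2/72)) = 3.25, and Φ(3.25 − 1.96) = 90.2%. The comparator is 85.1% from step 1. Any further gain from the stratum is not counted.

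Once enrolment BIAS is in the model, the treatment coefficient is the same whether the outcome is follow-up BIAS or its change. The planned 10-point difference therefore carries over unchanged.

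**The case against.** A reader might infer that the trial will be decided by a logistic model of BIAS and that its power is really 66% or lower. The article does not support that. The logistic sentence refers to outcome parameters in general and never mentions BIAS, no BIAS dichotomy appears anywhere, and a t-test is among the named methods. The t-test on change estimates the planned quantity and keeps the planned power. The figures in step 3 describe an analysis that the text permits but does not announce, and their cuts are assumptions.

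A reader might also infer that baseline BIAS and the stratum are excluded or ignored. They are not. The covariates are offered as examples, a full list may stand in a plan that is not shown, and a change score already subtracts the baseline. Analysing change instead of ANCOVA is valid, only less efficient. Leaving out a stratification factor usually makes the inference conservative.

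The text also separates normal from non-normal data just before it names the tests, so a loose rule for t-test or Mann–Whitney is implied.

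All of this stands, and it limits the point, but it does not remove the mismatch. Applying the logistic sentence to the secondary outcomes alone does not help either: quality of life, BDI and mRS are scores or ordinal scales, and the article defines no cut for them. No adjusted model suited to the primary endpoint is named.

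**Conclusion.** The point holds in a limited form. The article fixes a mean difference as its target, does not say which analysis decides it, and names as its only adjusted model one that cannot estimate it. This is a fault in what the text states, not an omission that a condensed article may leave to a later plan.

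Its size depends on how the text is carried out. With a t-test on change there is no shortfall against 85%. Compared with ANCOVA, about 5 to 8 points of power are forgone for r between 0.7 and 0.5 (90.2 − 85.1 = 5.1; 93.4 − 85.1 = 8.3). Only dichotomising BIAS would bring power well below plan.

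These figures rest on an SD of change of 20, on an assumed correlation and on equal SDs at both visits. None of these is in the article. The equal-SD assumption may be doubtful on a bounded scale in patients recovering from acute stroke, and the ANCOVA gain would change with it.

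**What to change.** Name one primary analysis before outcome data are seen: a linear model (ANCOVA) of BIAS percentile rank at the primary time point, which the same sentence should specify, on treatment group, enrolment BIAS percentile rank and the aphasia-severity stratum used in randomisation. Report the adjusted mean difference with its 95% CI. State that logistic regression applies only to outcomes whose dichotomy is defined in advance, and give those definitions.

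Robust or bootstrap standard errors, because the score is bounded, and a Mann–Whitney sensitivity analysis are optional additions.

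The cost is wording in the protocol and analysis plan. BIAS at enrolment and the stratum are already recorded, so no patients, visits or measurements are added.

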### Interventional Methods

Patients will be screened and assessed for eligibility directly after admission to our stroke unit. Patients eligible for entry to the study will be randomized and assigned to one of the two treatment arms after written informed consent. Each group (standard speech therapy vs. speech therapy with the therapist app version of Neolexon® therapy) should have a minimum of 50 participants. Because of the dropout rate of ~20%, at least 70 patients should be included in each group.

Each study arm (treatment group and control group) with a duration of 4 weeks includes three study visits. Follow-up will be assessed after 3 months (study visit 4). Figure 1 shows the study scheme and Table 2 demonstrates the schedule of enrollment and assessment as well as interventions at each study visit during the Lexi study.

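### The adjusted model admits complications and therapy arising after randomisation, so its group coefficient may not estimate the effect of assignment

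*Protocol article*

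**What the plan says.** The Primary Objective section introduces the regression with "Binary logistic regression models will be used to analyze the association between study group and outcome parameters". The next sentence reads "Results will be adjusted for well-known outcome predictors after stroke, e.g., age, sex, NIHSS, pmRS, lesion size, treatment, comorbidities, and complications". The list is open, no item carries a measurement time, and the article does not define which treatment or which complications are meant.

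On timing, Interventional Methods says "Patients will be screened and assessed for eligibility directly after admission to our stroke unit". Table 2 puts randomisation in the enrolment column (day 0 + 3 days), the end of intervention at day 28 ± 3 and the last visit at 3 months ± 7 days. The text after Table 2 adds "The total study duration is 12 weeks and is divided into three parts".

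Two further places bear on the word treatment. Data Analysis says the case report form captures how much and how often speech therapy and self-training were applied. The Discussion says the study will show whether the app raises motivation and, through it, the amount of self-training.

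The Primary Objective section also provides unadjusted comparisons (chi-square, Mann–Whitney, t-test). It does not say whether the adjusted model is primary or supportive.

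**The concern.** Randomisation protects the comparison of groups on anything fixed before allocation. A covariate that assignment can change is different in two ways. Conditioning on it removes whatever part of the effect runs through it. If it also shares unmeasured causes with the outcome, conditioning on it upsets the balance that randomisation created. The adjusted group coefficient then answers a different question from whether assignment to the app helps.

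Here the rule as written names two such candidates. Complications is the plainer one, because it is listed outright and without limit. Treatment is ambiguous, but it would matter most if it takes in speech therapy or self-training received, because the investigators themselves propose more self-training as a route by which the app works. At stake is whether the adjusted result can be read as an effect of assignment at all, in a trial where "we considered a 10% mean difference in the change of the PR of BIAS to be a minimal and clinically important difference".

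**Working it through.** **1. Timing.** Twelve weeks are 12 × 7 = 84 days. With randomisation as late as day 3, 84 − 3 = 81 days follow allocation, and 81/84 = 96% of the period counted from day 0. Up to visit 3 the figure is (28 − 3)/28 = 89%. So an unrestricted complications variable covers a window that lies almost wholly after allocation. This describes the window. It does not count events, and the article gives no event counts.

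**2. Which listed covariates can change after allocation.**
- Age, sex, premorbid mRS and pre-existing comorbidities: no.
- Lesion size: not if taken from baseline.
- NIHSS: measured at enrolment and at all four later visits; the enrolment value is fixed before or at allocation.
- Treatment: no, if it means acute stroke treatment given before randomisation; yes, if it includes therapy received afterwards.
- Complications: yes, unless limited to events before randomisation. Table 2 has no row for them.

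**3. Scale.** The stated sample size is not an input to this point, but it gives a scale. The article states no SD. From 72 analysed per group, a difference of 10 points, 85% power and a two-sided 5% test, the implied SD is 10 / (√(2/72) × (1.960 + 1.036)) = 20.0. Then 72/0.8 = 90 recruited per group, as stated.

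**4. Illustration A: complications lower the score (all inputs assumed).** Linear outcome, loss of 20 percentile-rank points per complication. Adjusted coefficient = total effect − 20 × (control rate − app rate).
- 30% control, 20% app: 10 − 20 × 0.10 = 8.
- 40% control, 25% app: 10 − 20 × 0.15 = 7.
- 30% in both: 10 − 0 = 10.
- Reversed, 20% control, 30% app: 10 + 20 × 0.10 = 12.

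**5. Illustration B: complications only share an unmeasured cause with the outcome (all inputs assumed).** Simulated with 500,000 patients per setting: outcome = effect × group − 10u + noise, total SD about 20; log-odds of a complication rise by 1 per unit of u. The complication itself has no effect on the score. The control rate is 33% throughout.

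| App rate | Adjusted, true effect 10 | Adjusted, true effect 0 |
|---|---|---|
| 33% | 10.0 | 0.05 |
| 29% | 9.6 | −0.4 |
| 24% | 9.3 | −0.8 |
| 19% | 8.8 | −1.1 |

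The unadjusted estimates stayed within 0.1 of 10 or 0. So a shift can appear even when the therapy has no effect on the score, provided assignment changes the complication rate.

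**6. Treatment read as therapy received.** If a fraction f of a 10-point effect runs through the amount of self-training, a linear model that adjusts for that amount (and has no other confounding) returns 10 × (1 − f): 10 when f = 0, and 0 when f = 1. The article gives no basis for choosing f.

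**7. Limits of the illustrations.** The only regression named is binary logistic, which yields odds ratios, not percentile-rank points. The conditioning problem carries over; the point values do not. Odds ratios also move when a purely baseline predictor is added, so a gap between adjusted and unadjusted odds ratios would not by itself show this bias.

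**The case against.** The strongest reply is that the sentence describes established predictors of outcome after stroke, lists them beside age, sex and premorbid mRS, and is meant as baseline adjustment. On that reading treatment is acute stroke treatment, and the rest is detail for an analysis plan that is not shown. This has force for treatment, which is ambiguous rather than shown to be wrong. It has less force for complications: naming them as a covariate is a choice made in the text, and the text does not restrict it.

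It is also fair to say that nothing in the article suggests a speech-therapy app changes complication rates. If it does not, there is little or no shift from complications.

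A reader might infer four stronger things that the document does not support:
- **That most complications follow allocation.** The schedule makes this plausible, but no section says so, and some may occur before randomisation within the enrolment window.
- **That a follow-up NIHSS will be the covariate.** The time point is unstated, but the enrolment value is collected and the list reads as baseline. Naming the enrolment value is a clarification, not a separate error.
- **That the main comparison is biased.** The primary objective is a difference in mean change in BIAS percentile rank. The adjustment sentence follows the logistic regression sentence and most naturally belongs to it, the adjusted model is not called primary, and the unadjusted tests do not use these covariates.
- **That the effect will be understated by 2 or 3 points.** Those figures come from assumed rates in a linear model, and the sign depends on which group has more complications.

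**Conclusion.** The point holds in a limited form. As written, the adjustment rule lets complications, and possibly therapy received, enter the treatment-effect model after allocation. If assignment affects those variables, the adjusted group coefficient does not estimate the effect of assignment; if it does not, little or no shift arises from this source.

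The size is unknown. Under the assumed inputs above, a total effect of 10 points becomes 7 to 8 when complications lower the score and the app group has fewer of them, and 8.8 to 9.6 when complications only share a cause with the outcome; with equal rates it stays at 10. The most serious case is treatment read as speech therapy or self-training received, because the Discussion proposes that pathway. The conclusion assumes no restriction elsewhere; an analysis plan that already fixes all covariates before randomisation would settle it.

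**What to change.** State in the analysis section that every covariate in the treatment-effect model is fixed before randomisation. From the existing list that means age, sex, enrolment NIHSS, premorbid mRS, baseline lesion size, pre-existing comorbidities, and acute stroke treatment given before randomisation. Replace the open list by a closed one.

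Take complications after randomisation, and speech therapy or self-training received, out of that model. Tabulate them by group, or use them only in an analysis labelled exploratory and not presented as the effect of assignment.

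The cost is a few lines of wording. The sample size, visit schedule and data collection stay as they are. The change should be made before the analysis is run.
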